### 2.8. Trial Oversight

The trial received a favourable opinion from the London—South East Research Ethics Committee (25/LO/0381). This study will be conducted in compliance with the principles of the Declaration of Helsinki (1996) and Good Clinical Practice (GCP). King’s College London and South London and Maudsley NHS Foundation Trust are the sponsors of this trial. The trial was registered with the ISRCTN registry (ISRCTN17989376, on 27 May 2025). Participant recruitment commenced in September 2025 and will continue until September 2026.

A Trial Steering Committee (TSC) will provide oversight throughout the duration of the trial. The TSC aims to ensure the trial is being conducted to GCP and other regulatory standards, that participant welfare is being considered in the design and running of the trial, and that sufficient progress is being made with regard to key milestones (e.g., participant recruitment).

### 2.9. Data Security and Management

The chief investigator will act as custodian for the study data. All study data will be stored in line with the Data Protection Act and archived in line with sponsor requirements. The source data for the study will be collected on paper case report forms (CRFs). Data will then be input into the trial database, which will be hosted on a secure server hosted within King’s College London. Access to the trial database will be restricted through user-specific passwords to authorised research team members. The database will only store pseudonymised data, not including any direct patient identifiers (e.g., name, date of birth, or contact information). Unique participant identification numbers (PINs) will be used within the database and paper CRFs. Paper forms will be stored securely within locked cabinets at each site.

The study team will undertake reviews of the entered data where appropriate for the purpose of data cleaning and will request amendments as required. Following checks of data correctness and completeness, all data will be formally locked for analysis.

### 2.10. Patient and Public Involvement (PPI)

A lived experience advisory panel (LEAP) comprising individuals with experience of unipolar or bipolar depression and lithium treatment will meet throughout the trial, to provide insight into the real-world impact of the trial activities, processes, and findings. The trial team also includes a PPI lead, who will be part of the TMG and lead the LEAP and co-authored this protocol. Patient-facing documents were reviewed by the Feasibility and Acceptability Support Team for Researchers (FAST-R), a team of people with lived experience of mental health problems and their carers who advise on research proposals and documentation.

### 2.11. Dissemination

The results of the trial will be reported in peer-reviewed scientific journals and presented at conferences. A primary publication will include all primary and secondary outcomes listed in the protocol. Further publications may report exploratory analyses. The results will also be disseminated to the public via plain English summaries, with input from the LEAP.

## 3. Discussion

This protocol describes a feasibility RCT which aims to test the utility of a novel POC testing method for lithium monitoring in the UK. Data gathered on feasibility, acceptability, and adherence to monitoring guidelines will be used to inform a larger confirmatory trial, which would establish whether POC testing is clinically effective and cost-effective. If POC testing is found to be effective in improving lithium monitoring in those with unipolar and bipolar affective disorders, this could lead to several benefits for this population. If there is an improvement in the proportion of time that participants’ lithium levels are kept within the therapeutic range, this could improve affective symptoms and reduce the side effects of lithium, enhancing quality of life. Further, POC testing may lead to direct and indirect cost benefits, for example, by eliminating the need for a separate appointment for a blood test and therefore reducing service use requirements and patient time off work. Further, prior research using POC testing for those taking antipsychotics has indicated that patients felt more involved in their own care and that receiving the test results almost immediately helped them understand the purpose of testing [17]. This could lead to improved engagement, trust, and communication between patients and their healthcare team.

This trial has a number of strengths and limitations. The trial will use a novel drug level monitoring method that has been shown to be acceptable and preferred over laboratory testing in a similar patient group [17]. Further, although this is a feasibility trial, the inclusion of five NHS sites across two regions of England will help improve the generalisability of the results, ensuring that the results are not an artefact of processes at one NHS trust. Although double-blinding is not possible in this trial (patients and at least some of the patient’s healthcare team would need to know their allocation), blinded-outcome raters will complete assessments for key clinical outcomes with patients to reduce bias. Related to this, it is possible that clinicians who are notified that their patient is taking part in a lithium monitoring trial will take more care to follow clinical guidelines for lithium monitoring. Measures to reduce contamination bias will be taken; for example, when patients’ clinicians are notified of their involvement in the trial, minimal detail on the intervention will be given to clinicians whose patients are in the TAU arm to reduce the chance that they will change their monitoring practices. They are told that the patient is taking part in a trial relating to lithium treatment but not that the trial relates to lithium monitoring. Further, a multi-method assessment of contamination bias is a primary objective of this trial, incorporating analyses of monitoring rates from patients before they entered the trial, comparing monitoring rates from exposed versus non-exposed services, changes in monitoring rates across the recruitment period, and feedback from clinicians.

Because this is a feasibility trial, inferences about efficacy cannot be made from the results. A further limitation of this trial is that we are only including patients who require 3-monthly monitoring, therefore excluding a large proportion of patients on lithium maintenance treatment who require monitoring every 6 months. This decision was made in order to have an adequate number of scheduled monitoring appointments per participant within the time constraints of a feasibility trial. If this trial is successful, we would hope to also include those on 6-month monitoring in the larger confirmatory trial that would follow, which may include a longer follow-up period. A 12-month follow-up period would allow for the inclusion of patients who require 3-monthly or 6-monthly monitoring, with 4 or 2 expected monitoring appointments within the trial follow-up period, respectively. This would also allow longer-term adherence and efficacy to be assessed. However, a 12-month follow-up period presents challenges with regard to research investment. Finally, although the POC testing method provides lithium and creatinine serum levels, it does not provide monitoring of other parameters that the clinician may require or are recommended while taking lithium, such as urea and electrolytes, calcium, and thyroid function. NICE guidelines recommend that these parameters be monitored every 6 months or more frequently in certain circumstances [1].

The quality of lithium monitoring in the UK and elsewhere is currently poor, potentially contributing to poor health outcomes in those with unipolar and bipolar affective disorders. Known issues with current blood monitoring practices may lead to patients being outside the therapeutic range for lithium, putting them at risk of relapse or sub-optimal symptom management if levels are too low or compromising physical health if levels are too high. The LiPOC trial aims to build on previous work introducing POC testing to psychiatry, with the hope of improving care and quality of life in this population. Further, despite lithium being the most efficacious drug for preventing mood episodes in bipolar disorder, the rates of prescribing are declining [27]. If POC testing is eventually adopted in healthcare services and is perceived by clinicians and patients as less burdensome and more efficient than laboratory testing, clinicians may be more likely to prescribe lithium to their patients, providing more patients with the chance to trial an effective treatment for their condition.

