### 2.6. Outcomes

Primary outcomes are as follows:Feasibility
Participant recruitment rates over the trial period.Participant retention and completion rates over 30 weeks.Rates of lithium discontinuation over 30 weeks.Adherence to lithium monitoring guidelines (proportion of participants meeting NICE guidelines for frequency testing and lithium levels within therapeutic range) over 30 weeks.
Patient acceptability
Patient monitoring acceptability questionnaires at week 15 and week 30.Patient preferences for POC testing versus laboratory testing.Perceived usefulness of POC monitoring.
Contamination bias
Monitoring rates between treatment-exposed versus non-exposed services.Changes in monitoring rates from first to last patients recruited.Participants’ monitoring rates from before trial (from electronic health records) versus during the trial.Clinician survey about service changes during the trial.

Secondary outcomes are as follows:Costs and economic outcomes
Health related-quality of life via the EuroQol-5D (EQ-5D) [21] at weeks 15 and 30.Service utilisation via the Client Service Receipt Inventory (CSRI) [22] at weeks 15 and 30.
Mood and affective symptoms
Manic symptoms via the YMRS at weeks 15 and 30 [19].Depression symptoms via the MADRS [23] at weeks 15 and 30.Depression, mania, and anxiety symptoms via the Maudsley visual analogue scales (M3VAS) [24] at weeks 15 and 30.
Side effects and adverse events
Lithium side-effects rating scale (LiSERS) [25] at weeks 15 and 30.Adverse events over 30 weeks.

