### 2.7. Statistics

The sample size of 80 will enable the estimation of a 50% dropout rate with a confidence interval of ±10% [26].

Variables will be summarised using descriptive statistics (i.e., mean and standard deviation [SD] or median and interquartile range [IQR] or frequencies and proportions, as appropriate). Recruitment, retention, discontinuation, and measure completion rates will be described. The number and proportion of participants meeting NICE guidelines [1] for test frequency and therapeutic range compliance (usually 0.6 mmol/L–0.8 mmol/L but in certain specified circumstances either 0.8 mmol/L–1.0 mmol/L or 0.4–0.6 mmol/L) will be reported between study arms. Because our aim is to take three measurements per participant within the 30-week trial period, we are recruiting patients who require 3-monthly monitoring (with measurements at baseline/week 0, week 15, and week 30). However, due to the practical timing of clinic visits, some participants may only complete two measurements within this period; therefore two or three measurements will be considered adherent to monitoring guidelines, as long as they align with the participant’s scheduled monitoring timeframes. Acceptability questionnaires will be described quantitatively within subjects and between groups over time, as well as a qualitative analysis of narrative response questions.

The following will be analysed descriptively to investigate potential contamination bias (i.e., mean and SD or median and IQR or frequencies and proportions, as appropriate): (a) monitoring rates between treatment-exposed vs. non-exposed services, (b) changes in monitoring rates from the first to last patients recruited, (c) participants’ monitoring history from electronic health records, and (d) ratings from surveying clinicians about practice changes during the trial.

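### Two of the four contamination measures are timed by participant entry and recruitment order, not by when a service first had a POC patient

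*Protocol article*

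**What the plan says.** Sections 2.6 and 2.7 of the Protocol article list four contamination measures. The Discussion restates them and calls contamination a primary objective.

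- **Services:** "monitoring rates between treatment-exposed vs. non-exposed services".
- **Trend:** "Changes in monitoring rates from first to last patients recruited" (2.6), repeated in 2.7 and restated in the Discussion as "changes in monitoring rates across the recruitment period".
- **Before/during:** participants' "monitoring rates from before trial (from electronic health records) versus during the trial" (2.6). Read alone, this could mean before the trial opened. The Discussion settles it as each patient's own entry: "incorporating analyses of monitoring rates from patients before they entered the trial".
- **Clinician survey** about changes in practice.

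The analysis is descriptive: "The following will be analysed descriptively to investigate potential contamination bias". Allocation is individual, 1:1, stratified by site (2.5). Participants come from any service in five trusts (2.2) and stay under their usual clinicians (2.1). Entry is staggered over about a year: "Participant recruitment commenced in September 2025 and will continue until September 2026" (2.8). As written, neither time-based measure is limited to TAU participants, dated from a service's first POC patient, or crossed with the exposed/non-exposed split.

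**The concern.** If contamination means that usual monitoring in a service shifts once POC patients are managed there, it starts for that service at its first POC allocation. The two time-based measures start elsewhere, and this can mislead in two ways.

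- **Before/during.** A TAU participant recruited late, in a service that already has a POC patient, brings a 'before' period that is partly exposed. Subtracting it removes some of the effect being looked for.
- **First to last.** Recruitment order is not exposure. A late recruit in a service with no POC patient is unexposed, while an early recruit in a service that already has one is exposed. With no concurrent comparator, a general change in monitoring, or a change in which sites supply recruits, enters the measure as if it were contamination.

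Hidden exposure lowers the before/during change, while upward drift raises both measures. Agreement between the two is therefore no reassurance. Because POC participants are not set apart, the intervention's own effect also enters the before/during change. At stake is the description of a stated primary objective.

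**Working it through.** The plan gives no figure for contamination, so there is none to reproduce. The check asks how far the two clocks can differ from the exposure clock.

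**Inputs from the article:** 80 participants, five trusts, 1:1 individual allocation, about 52 weeks of recruitment, 30 weeks of follow-up.

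**Assumptions:** even entry over 52 weeks; independent 1:1 allocation; *m* participants per service (not given); look-back of *L* weeks (not given). *m* = 16 is 80/5, a whole trust counted as one service.

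**Step 1. Participants who enter after their service's first POC allocation.** The *k*-th entrant has *k* − 1 predecessors, at least one of them POC with probability 1 − (1/2)^(*k*−1). Averaging over *k* = 1 to *m* gives 1 − (2/*m*)(1 − 2^(−*m*)). For *m* = 2: 1 − 1 × 0.75 = 25%. For *m* = 4: 1 − 0.5 × 0.9375 = 53%.

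**Step 2. Share of the look-back already exposed.** For a participant entering at week *t*, the chance that the service was exposed by week *t* − *s* is 1 − (1 − (*t* − *s*)/104)^(*m*−1). Average this over *s* from 0 to *L* (zero where *s* > *t*) and over *t* from 0 to 52.

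Worked case, *m* = 2, *L* = 30:
- *t* from 0 to 30: ∫ *t*²/208 d*t* = 27,000/624 = 43.3.
- *t* from 30 to 52: ∫ (30*t* − 450)/104 d*t* = 17,160/104 = 165.0.
- Share = 208.3/(30 × 52) = 0.134. A 20,000-run simulation of the same model gave 0.137.

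| Participants per service | Enter after first POC | Exposed share, 26-week look-back | 30-week | 52-week |
|---|---|---|---|---|
| 2 | 25% | 15% | 13% | 8% |
| 4 | 53% | 33% | 31% | 19% |
| 8 | 75% | 51% | 47% | 31% |
| 16 | 87.5% | 63% | 59% | 39% |

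**Step 3. Effect on the before/during change.** If exposure raises the monitoring rate by δ and a share *q* of the look-back is exposed, the 'before' rate is raised by *q*δ and the change is reduced by the same amount. For an assumed δ of 10 points and a 30-week look-back, the loss is about 1.3 points at 2 per service, 3.1 at 4 and 5.9 at 16.

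**Step 4. Shared drift with zero contamination.** Assume every service improves by 5 to 10 points a year.
- First to last, entries 52 weeks apart: 5 to 10 points.
- Before/during, with window midpoints 15 weeks either side of entry: 5 × 30/52 = 2.9 to 10 × 30/52 = 5.8 points.
- Exposed versus non-exposed over the same calendar period: 0.

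The Introduction shows that such rates do move for other reasons: 30% met the frequency guideline in 2009 and 48% after a national programme. That rise is evidence that drift happens, not a forecast for one recruitment year.

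**Step 5. Site mix.** If site rates are constant but sites contribute different shares *w* of early and late recruits, the apparent change is Σ (*w*_late − *w*_early) × rate, summed over sites. It is generally not zero when site rates differ.

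**The case against.** The strongest reply has five parts.

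1. **Entry is the right clock for one mechanism.** The Discussion concedes that a clinician told of a patient's participation may follow guidelines more closely. That effect starts at the patient's entry. This stands, and it is why the entry-anchored rate should be kept.
2. **Exposure may be weak.** A researcher brings the device to the test (2.4.1), and clinicians of TAU patients are not told that the trial concerns monitoring. This bears on how large contamination is, not on when it could start.
3. **The four measures are meant to be read together.** The exposed/non-exposed comparison and the survey can help separate drift from contamination. This stands in part: the article gives no exposure date and does not combine that comparison with the time-based measures.
4. **Details belong in the full protocol or SAP.** Look-back length and cross-tabulations may well be there, and their absence is not the point. The article does state the reference points themselves, in its primary outcomes and Discussion.
5. **The size is unknown.** This stands. Overlap needs at least two participants in a service and is modest if services are very small.

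A reader might go further and count all history after trial opening as exposed. The documents do not support that, since a service is exposed only from its own first POC patient. Nor do they support false-positive rates for a trend test, because the analysis is descriptive and no such test is planned.

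**Conclusion.** The concern holds in limited form. As stated, the before/during measure can understate contamination in services with more than one recruit, and the first-to-last measure cannot separate contamination from shared drift or site mix.

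For a 30-week look-back, the exposed share runs from about 13% at 2 participants per service to 59% if a trust is one service. Across look-backs of 26 to 52 weeks the range is 8% to 63%. These figures rest on even entry, independent 1:1 allocation and assumed service sizes. The drift of 5 to 10 points is likewise an assumption.

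A reader might infer that these results will decide between randomising individuals and randomising services. The article does not say so: its Discussion says only that feasibility, acceptability and adherence data will inform a confirmatory trial, and Table 2 has no contamination criterion. What is affected is the quality of the answer to a stated primary objective.

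**What to change.** - **Date exposure.** Record each service's first POC allocation date, from the randomisation log and each participant's service.
- **Before/during.** Keep the entry-anchored rate, which suits the clinician-notification effect. Report it for TAU participants separately, split by whether the look-back falls before or after that date.
- **Recruitment-period change.** Report TAU monitoring before versus after the service's first POC allocation, beside services not yet exposed over the same calendar periods. Base the contamination reading on that contrast, not on the raw trend.

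The cost is analysis wording and one date per service, with no added patients or visits. The downside is real but manageable. Some cells will be small. Participants who started lithium recently will have little history before exposure, and the three-monthly eligibility rule makes them likely recruits, because the Introduction links that frequency to the first year of treatment. They should be counted and shown separately.

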## Figures and Tables

**Figure 1 pharmaceuticals-18-01683-f001:**
[figure not shown]
Study flowchart.

**Figure 2 pharmaceuticals-18-01683-f002:**
[figure not shown]
Summary of patient visits and assessments. Blue indicates screening (pre-study), green indicates baseline and follow-up period.

**Table 1 pharmaceuticals-18-01683-t001:** Study procedures by visit.

Procedures/Measures	Screening (Pre-Study)	Baseline (W0)	Follow-Up 1 (W15)	Follow-Up 2 (W30)
Informed consent process	X	X		
Medical and psychiatric information	X	X		
Sociodemographic information	X	X		
Medication and lithium review	X	X	X	X
Randomisation		X		
EuroQol-5D (EQ-5D)		X	X	X
Client Service Receipt Inventory (CSRI)		X	X	X
Young Mania Rating Scale (YMRS)	X	X	X	X
Montgomery–Åsberg Depression Rating Scale (MADRS)		X	X	X
Maudsley visual analogue scales (M3VAS)		X	X	X
Lithium side-effects rating scale (LiSERS)		X	X	X
Patient monitoring acceptability questionnaire		X	X	X
Participant end of study feedback questions				X

**Table 2 pharmaceuticals-18-01683-t002:** Go–no-go criteria to be met to proceed with an efficacy trial.

	Go—Proceed with RCT	Amend—Proceed with Changes	Stop—Do Not Proceed Unless Changes Are Possible
Participant recruitment	80 in 12 months	80 reached but in >12 months	53 not reached by 12 months
POC monitoring acceptability	≥80% rating POC as “acceptable”	30–79% rating POC as “acceptable”	<30% rating POC as “acceptable”
Participant attrition rate	≤20% attrition	21–50% attrition	>50% attrition
Adherence to lithium monitoring guidelines	>60% adherence	30–60% adherence	<30% adherence

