## Abstract

Lithium is the first-line treatment for bipolar disorders and a first-line augmentation option for treatment-resistant unipolar depression. Due to its narrow therapeutic window and risk of toxicity, people taking lithium require regular blood testing to monitor lithium levels in the body. However, studies have reported that only half of lithium-treated patients receive adequate lithium monitoring. This protocol describes a trial that will test the feasibility and acceptability of a point-of-care (POC) lithium blood testing programme in patients with unipolar or bipolar affective disorders taking lithium as a maintenance treatment. The primary objectives are to establish whether testing the effectiveness of POC testing is feasible, by assessing recruitment, attrition, and adherence to monitoring guidelines compared to participants randomised to testing as usual; to test whether the programme is acceptable to patients; and to measure potential contamination bias. The secondary objectives are to examine changes in health-related quality of life, the use of healthcare services, and depressive and manic symptoms to inform the design of a larger multi-site randomised controlled trial (RCT). This feasibility RCT will recruit 80 participants with affective disorders who are taking lithium. Participants will be 1:1 randomised to either POC monitoring or monitoring as usual where they will be followed up at three research visits over 30 weeks. The proportion of patients meeting guidelines for lithium monitoring will be examined, alongside measures of acceptability, wellbeing, and health economic data. POC testing has the potential to significantly improve patient safety and satisfaction with lithium treatment.

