The unit costs of the intervention and use of other services will be estimated with the CSRI and compared between groups to identify the main cost impacts that should be measured in a future trial, in combination with health-related quality of life data from the EQ-5D to estimate quality-adjusted life years (QALYs). Generalised linear mixed models will estimate the between-arm differences at 15 and 30 weeks for the M3VAS, YMRS, MADRS, and LiSERS. These analyses will be used to estimate effect sizes for a future definitive RCT, as this feasibility RCT is not powered to detect treatment differences. The generalised linear mixed models will use all available data under a maximum likelihood framework. Missing follow-up data will not be imputed. Adverse events will be summarised descriptively between arms.

Analyses will be intention to treat (ITT). Sensitivity analyses may be carried out, excluding participants without clear information on their lithium treatment or monitoring.

Table 2 details key feasibility criteria to be met to proceed with a larger definitive RCT.

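### The Table 2 recruitment row gives no outcome if 53–79 are recruited and 80 is never reached, and two outcomes if fewer than 53 at 12 months later become 80

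*Protocol article*

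**What the plan says.** The target is fixed in the Abstract: "This feasibility RCT will recruit 80 participants with affective disorders who are taking lithium". Section 2.6 lists recruitment first among the primary feasibility outcomes: "Participant recruitment rates over the trial period". Section 2.7 gives Table 2 its role: "Table 2 details key feasibility criteria to be met to proceed with a larger definitive RCT".

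The recruitment row of Table 2 has three cells:

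- Go: "80 in 12 months"
- Amend: "80 reached but in >12 months"
- Stop: "53 not reached by 12 months"

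Section 2.8 sets the calendar: "Participant recruitment commenced in September 2025 and will continue until September 2026". The article states no extension procedure and no rule for which cell prevails if two apply.

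**The concern.** A three-level progression rule should place every possible result in exactly one level. This row does not, because its cells are measured on different scales. Go and Stop look at how many have been recruited when 12 months have passed. Amend asks whether 80 is ever reached, with no outer limit.

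A moderate shortfall is the kind of result for which a middle category exists. If recruitment closes on the stated date with such a shortfall, the rule is silent, and the category would have to be chosen once the number is known. In the other direction, a slow trial that is extended until it reaches 80 satisfies two cells at once. Settling these cases in advance is the purpose of pre-stated progression criteria.

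**Working it through.** The row states no probability or expected count, so there is no figure of the plan's own to reproduce. The check has two parts: the logic of the rule, and how often the gap might matter.

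**1. Enumerating the rule.** Inputs from Table 2: target 80, lower limit 53, time point 12 months. Let *n* be the number recruited by 12 months. Go applies if *n* ≥ 80; Amend if *n* < 80 and 80 is reached later; Stop if *n* < 53. Every *n* from 0 to 80 was run through these conditions.

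| Recruited by 12 months | 80 never reached | 80 reached later |
|---|---|---|
| 0–52 (53 counts) | Stop | Stop and Amend |
| 53–79 (79 − 53 + 1 = 27 counts) | no cell | Amend |
| 80 | Go | Go |

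The gap is the middle cell of the first outcome column. The overlap is the top cell of the second.

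**2. Fit with the calendar.** Section 2.8 gives months, not days. The window is about 12 months and at most about 13 (start of September 2025 to end of September 2026). If recruitment closes as planned, Amend could be met only within that small slack. Otherwise the row reduces to Go, Stop or nothing.

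**3. Comparison with the other rows.** Acceptability (≥80, 30–79, <30%), attrition (≤20, 21–50, >50%) and adherence (>60, 30–60, <30%) each use adjoining bands on one scale. In whole percentages they have no gap or overlap. Only the recruitment row departs from this pattern.

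**4. How likely is a 12-month count of 53–79?** The article gives no expected rate, so this needs an assumption: the 12-month count *X* is Poisson with mean *m*, for *m* from 40 to 100.

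P(53 ≤ X ≤ 79) = Σ e^(−m) m^k / k!, summed over k = 53 to 79.

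| Assumed mean | P(<53) | P(53–79) | P(≥80) |
|---|---|---|---|
| 40 | 0.972 | 0.028 | 0.000 |
| 50 | 0.646 | 0.354 | 0.000 |
| 53 | 0.482 | 0.518 | 0.000 |
| 60 | 0.167 | 0.826 | 0.008 |
| 66.7 | 0.037 | 0.901 | 0.062 |
| 70 | 0.015 | 0.856 | 0.129 |
| 75 | 0.003 | 0.700 | 0.297 |
| 80 | 0.001 | 0.485 | 0.515 |
| 90 | 0.000 | 0.133 | 0.867 |
| 100 | 0.000 | 0.017 | 0.983 |

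At a mean of 66 the middle probability is also 0.90. The 53–79 band is the most probable of the three for means from about 53 to just under 80, and not outside that range. These are probabilities of being at 53–79 at 12 months. They equal the probability of having no category only if recruitment then stops short of 80.

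**5. Check of the repaired row.** With Go ≥ 80, Amend 53–79 and Stop ≤ 52, all read at 12 months, the 81 counts from 0 to 80 split as 1 + 27 + 53 = 81. Each is classified once, and counts above 80 fall in Go.

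**The case against.** The strongest reply is that the row assumes recruitment runs to its target. The trial is planned to recruit 80, and the Amend cell itself speaks of taking longer than 12 months, so a trial at 53–79 after a year simply carries on and becomes Amend on reaching 80. The Trial Steering Committee is charged with watching recruitment milestones, and an extension procedure may sit in the full protocol, which is not shown. This stands in part: 53–79 at 12 months is not always without an outcome. It does not cover a trial that closes on the date in Section 2.8 or never reaches 80, and it leaves the overlap untouched.

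A second reply is that little turns on the overlap. The Stop column is headed as not proceeding unless changes are possible, and the Amend column as proceeding with changes, so both leave a route forward. The Stop check also falls earlier in time. This reduces the consequence, but no precedence is stated.

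A third is that recruitment is one of four rows, is reported descriptively whatever its label, and has both outer limits fixed in advance, so a count between them is plainly neither Go nor Stop. That is fair, and it bears on severity.

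A reader might also infer that the most likely results cannot be classified. The article does not support this. It states no expected recruitment rate; the probability of 53–79 ranges from 0.02 to 0.90 over the assumed means; extension to 80 would classify those counts; and the overlap case is classified twice rather than left out.

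**Conclusion.** The point holds as a defect in a stated decision rule. It is not a matter of detail left to another document, since the article prints the criterion in full. Mixing a 12-month count with an open-ended condition leaves 27 totals (53–79) without an outcome whenever 80 is never reached, including on closure in September 2026 as planned. It gives two outcomes when fewer than 53 at 12 months later become 80. These conclusions follow from the wording of Table 2 and need no distributional assumption.

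How often the gap would matter cannot be settled from the article. The probabilities in the working rest on an assumed Poisson count and on recruitment not being extended to 80.

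This should be fixed, but it is not critical. No estimate, analysis or participant is affected, it is one progression row of four, and Stop itself permits proceeding if changes are possible.

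**What to change.** Restate the recruitment row on one quantity, participants randomised by 12 months, using the thresholds already in Table 2:

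- Go: 80 or more
- Amend: 53–79
- Stop: fewer than 53

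Add that a Stop reading at 12 months takes precedence over any later total, and that if recruitment is extended, the time taken to reach 80 is reported descriptively. Agree the change with the Trial Steering Committee before recruitment closes.

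The cost is one table row and no extra data. There is one change of substance to accept openly: Amend now requires 80 to be reached in the end, and under the new row 53 at 12 months would be enough. If the sponsor wishes to keep the requirement to reach 80, the row needs a stated time limit for doing so, an outcome for 53–79 when that limit passes, and a precedence rule for counts below 53.
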